## Background

Discectomy is the most common surgical method for resolving lumbar radiculopathy caused by disc herniation and nerve root compression [1, 2]. Currently, microscopic discectomy is performed as minimally invasive surgery, reducing the invasiveness of conventional open discectomy [3–5]. Minimally invasive spinal surgery has been developed by using a tubular retractor, microscope, and endoscope to achieve effective neural decompression while preserving the stabilizing structures of the spine [4–7]. Although technically more demanding, interlaminar full-endoscopic discectomy has significantly reduced surgical invasiveness, thereby expanding the indications for endoscopic surgery [5, 8–10]. Specifically, interlaminar full-endoscopic discectomy offers several advantages over conventional microscopic discectomy, including a smaller skin incision and, thus, less scarring and less muscle damage, a lower infection rate and volume of blood loss, a less painful recovery, and a shorter hospital stay [3, 11–17]. Previous studies have reported no differences in clinical outcomes between interlaminar endoscopic and microscopic discectomy [18–22]. However, the evidence regarding the efficacy and safety of interlaminar full-endoscopic discectomy compared with those of microscopic discectomy is limited by the small sample size in these studies and type of research design, namely retrospective, single-center prospective designs [7, 18–25]. Therefore, a multicenter, randomized controlled trial (RCT) is warranted.

To address this gap in evidence, we propose a multicenter, prospective RCT to compare the outcomes of interlaminar full-endoscopic discectomy versus those of microscopic discectomy. Our guiding hypothesis is that the efficacy and safety of interlaminar full-endoscopic discectomy and microscopic discectomy of the lumbar spine will be similar.

In addition to the findings from previous studies, if this non-inferiority RCT with a high evidence level shows no differences in the primary outcomes of neural decompression between the two discectomy surgeries, these results, combined with less invasiveness of interlaminar full-endoscopic discectomy may suggest that interlaminar full-endoscopic discectomy is a superior alternative to conventional open surgery.

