## Methods/design

### Trial design

This study aims to evaluate the non-inferiority of the outcomes of interlaminar full-endoscopic discectomy versus those of microscopic discectomy using a multicenter RCT design. Our methods have been approved by the institutional review boards of the participating hospitals (The Catholic University of Korea Seoul St Mary’s Hospital; Kyung Hee University Medical Center; Chungdam Wooridul Spine Hospital; Wiltse Memorial Hospital; Seoul National University Bundang Hospital; Kangnam Sacred Heart Hospital; and The Catholic University of Korea Daejeon St. Mary’s Hospital).

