
### Statistical analyses

All statistical analyses will be performed using SAS Enterprise Guide 4 (SAS Institute Inc., Cary, North Carolina, USA). Before performing the main comparative statistical analyses, we will assess whether the baseline variables of the two groups are visually balanced.

An intention-to-treat strategy will be implemented in this non-inferiority RCT. In addition, sensitivity analyses using per-protocol and As-treated will be conducted to identify the deviations from the original assignments during randomization. Participants excluded before or after surgery will not be considered for analysis or replaced, thus avoiding the risk of bias in allocation concealment.

The primary outcome (the ODI score at 12 months post-surgery) will be compared between the two groups. Interlaminar full-endoscopic discectomy will be considered equivalent to microscopic discectomy concerning surgical outcomes if the 95% confidence interval (CI) of the treatment difference value of the Interlaminar full-endoscopic discectomy group is included in the equivalence limit of 12.8 points.

To analyze the time-dependent change in secondary patient-reported and clinical outcomes (i.e., VAS pain scores for the back and lower extremities and ODI, EQ-5D, and POSAS scores), a linear mixed model repeated-measures analysis of variance will be used. Time will be regarded as a categorical variable (at 2 weeks and at 3, 6, and 12 months) and analyzed to evaluate serial changes from baseline, within each group, and between the two groups at each session, with a post hoc test used for any significant time- and group-differences identified.

Chi-square test for categorical variables and Student’s t-test for continuous variables will be used to analyze other clinical and radiographic outcomes and adverse effects between the two groups. The collected data’s distribution will be evaluated using the Shapiro–Wilk test, with a two-sided P-value. Normally distributed continuous variables will be reported as means and standard deviations (SDs), with non-normally distributed continuous variables reported as medians and interquartile ranges. Categorical variables will be reported as count and percentage (%).

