### Sample size justification

In this trial, 100 participants will be recruited, with 50 in each group. Based on previous studies by Copay et al., the non-inferiority margin is 12.8 points and the maximal clinically accepted ODI difference is 12.8 points, with an SD of 17.1 points at 1-year after endoscopic discectomy [21, 35]. Based on the non-inferiority margin of 12.8, 50 participants will be required in each group, with an alpha value of 0.05, a power of 0.90, a one-sided 95% CI, and a loss to follow-up of 20%. Power Analysis and Sample Size software (version 15; NCSS, Kaysville, UT, USA) was used to calculate the sample size.

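### The trial is declared and sized as non-inferiority, but its only primary decision rule is an equivalence rule; on the ordinary reading that rule has about 82% power, not 90%, and can fail a better endoscopic result

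*Protocol article*

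**What the plan says.** The objective is stated under Trial design: "This study aims to evaluate the non-inferiority of the outcomes of interlaminar full-endoscopic discectomy versus those of microscopic discectomy". The Background and the analysis section use the same label; Statistical analyses says "An intention-to-treat strategy will be implemented in this non-inferiority RCT".

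Sample size justification follows that objective. It says "the non-inferiority margin is 12.8 points", takes the variability from earlier data ("with an SD of 17.1 points at 1-year after endoscopic discectomy"), and concludes: "Based on the non-inferiority margin of 12.8, 50 participants will be required in each group". The other inputs there are alpha 0.05, power 0.90, a one-sided 95% CI and 20% loss to follow-up.

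The rule that decides the primary outcome, in Statistical analyses, is of another kind: "Interlaminar full-endoscopic discectomy will be considered equivalent to microscopic discectomy concerning surgical outcomes if the 95% confidence interval (CI") of the treatment difference "is included in the equivalence limit of 12.8 points". It does not give the sidedness of the interval, does not write ± before the limit, and does not say which confidence limit decides. No other criterion for the primary outcome is given.

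**The concern.** Non-inferiority asks one question: is the endoscopic procedure worse by less than the margin? A higher ODI means more disability, so for the difference endoscopic minus microscopic only the upper confidence limit matters. Equivalence also requires the lower limit to stay above −12.8, which means that endoscopy must not be too much better. One dataset can therefore pass the declared objective and fail the written rule.

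Two things are at stake. First, the 90% power is stated for a non-inferiority design and need not apply to the rule that will be used. Second, with both labels in print and the sidedness open, the same result could be called a success or a failure once it is known. The second limit also works against the trial's purpose, which is to support endoscopy as an alternative: the better endoscopy performs, the more likely the rule is to fail.

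**Working it through.** **Inputs.** From Sample size justification: margin M = 12.8, SD = 17.1, power 0.90, 20% loss, 50 per group, so 50 × 0.8 = 40 evaluable per group. Allocation is 1:1 (Randomization and follow-up). The article gives no true difference d; I assume d = 0, in line with the Background hypothesis that the procedures are similar.

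**Step 1: the plan's own figure.** For d = 0 the normal approximation is n per group = 2·SD²·(z₁ + z₂)² / M², and 2 × 17.1² / 12.8² = 3.569. For non-inferiority z₁ + z₂ = z(1−α) + z(0.90). For equivalence with d = 0, z(0.90) is replaced by z(0.95), because the 10% chance of failure is split between two limits. The t-based counts come from the non-central t distribution (non-inferiority) or integration over the sample variance (equivalence).

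| Test | Normal approximation | Evaluable per group (t) | Divided by 0.8 |
|---|---|---|---|
| Non-inferiority, one-sided 0.05 | 3.569 × (1.645 + 1.282)² = 30.6, so 31 | 32 | 40 |
| Non-inferiority, one-sided 0.025 | 3.569 × (1.960 + 1.282)² = 37.5, so 38 | 39 | 49 |
| Equivalence, 90% CI (two tests at 0.05) | 3.569 × (1.645 + 1.645)² = 38.6, so 39 | 40 | 50 |
| Equivalence, two-sided 95% CI | 3.569 × (1.960 + 1.645)² = 46.4, so 47 | 48 | 60 |

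The stated 50 is not what the literal one-sided 0.05 non-inferiority inputs give (40). It is within one patient of non-inferiority at 0.025 and matches equivalence with a 90% CI exactly. The number alone does not show which test was used.

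**Step 2: power with 40 evaluable per group and d = 0.** SE = 17.1 × √(2/40) = 3.824, and M/SE = 12.8 / 3.824 = 3.348.

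- Upper limit of a two-sided 95% CI only: Φ(3.348 − 1.960) = 0.917; t version 0.911.
- One-sided 95% upper bound only: Φ(3.348 − 1.645) = 0.956; t version 0.953.
- Equivalence, 90% CI within ±12.8: 2Φ(1.703) − 1 = 0.911; t version 0.906.
- Equivalence, two-sided 95% CI within ±12.8: 2Φ(1.388) − 1 = 0.835; t version 0.822.

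With no dropout (50 evaluable per group), the last rule has power 0.919 (t).

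**Step 3: where a better result fails.** With 78 degrees of freedom t = 1.991, so the half-width of the 95% CI is 1.991 × 3.824 = 7.61, if the observed SD is 17.1. The lower limit passes −12.8 once the observed endoscopic advantage exceeds 12.8 − 7.61 = 5.19 points. At that advantage the upper limit is −5.19 + 7.61 = +2.4, far below +12.8.

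**Step 4: illustration.** Suppose endoscopy is truly 5 points better, a value that is mine and not the plan's. With 40 evaluable per group, the two-sided 95% equivalence rule succeeds in 52% of trials and the 90% CI version in 65%. The upper-limit rule at one-sided 0.025 succeeds in over 99%.

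**The case against.** The strongest reply is that 82% rests on words the article does not contain. The decision rule says neither two-sided nor ±, and the only sidedness given anywhere is the one-sided 95% CI in Sample size justification. Of the four readings in step 2, three keep power at or above 90%, and the fourth recovers to about 92% with no dropout. The planned 50 per group also fits an equivalence calculation with a 90% CI at least as well as a non-inferiority one. A reader might infer that the trial is plainly underpowered, or that the number was certainly derived for non-inferiority. The documents support neither as a flat statement. This part of the objection stands, and the power figure is therefore given as a range.

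A reader might also take the Background remark, "if this non-inferiority RCT with a high evidence level shows no differences in the primary outcomes of neural decompression", as a further success criterion. It is conditional prose about what the findings may suggest, not a decision rule, and no weight is put on it.

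It can further be said that the article hypothesises similarity, so a true advantage of 5 points is hypothetical, and that at the same test level equivalence is the stricter claim: any result that meets it also meets non-inferiority. Both are right. The written rule does not inflate false claims of non-inferiority; its cost is lost power and an undefined conclusion.

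What the objection does not remove is the mismatch itself. It is present within Statistical analyses alone, and it is not detail left to an unseen analysis plan, because the article does state a primary decision rule. That four readings are possible shows that the rule is not fixed.

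**Conclusion.** The point holds in this form: the declared objective is non-inferiority, the only primary decision rule is equivalence, and test level and sidedness are not reconciled between Statistical analyses and Sample size justification. That conclusion needs no assumption.

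Its size is conditional. On the ordinary reading of a 95% CI lying inside an equivalence limit, with SD 17.1, the full 20% loss and a true difference of 0, power is about 82% instead of 90%. Across the other readings it is about 91% to 95%. The penalty on a better endoscopic result belongs to any two-limit reading and is absent only if the upper limit alone decides.

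**What to change.** In Statistical analyses, replace the equivalence sentence with a one-limit rule: endoscopic discectomy is non-inferior if the upper limit of the CI for the mean 12-month ODI difference, endoscopic minus microscopic, is below +12.8 points. Drop equivalence as the conclusion.

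State the same alpha and sidedness there and in Sample size justification. A two-sided 95% CI (one-sided 0.025) is one consistent choice: it needs 39 evaluable, or 39 / 0.8 = 48.75, so 49 per group, and the planned 50 covers it. Changing the analysis section alone would leave the one-sided 95% CI in the sample-size section in conflict with it.

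If equivalence with a two-sided 95% CI is really intended, call the trial an equivalence trial throughout, write the limits as ±12.8, and restate the power as about 82% at 40 evaluable per group. Keeping 90% power would take 48 evaluable, or 48 / 0.8 = 60 per group (120 in total).

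The non-inferiority route costs wording only. It should be settled before outcome data are compared by group.

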### Inclusion criteria

The inclusion criteria are as follows: patients for whom conservative treatment has failed and who are considered suitable for decompression surgery; age, 20–80 years; diagnosis of single-level lumbar disc herniation; radiating pain to the lower extremities, with a pain score > 4 on a 10-point visual analog scale (VAS); lumbar disc herniation cases wherein both interlaminar full-endoscopic discectomy and conventional microscopic discectomy are considered possible and appropriate by an operator; ability to follow instructions and to provide consent for participation; and willingness to comply with the trial’s follow-up protocol. The following types of disc herniation will be included: protruded, extruded, and migrated types of disc herniation in the central canal and subarticular zones [26].

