### Data collection

After providing informed consent, participants will be enrolled in the study and will undergo baseline assessments, including the following: magnetic resonance images (MRIs), simple radiographs, the Oswestry Disability Index (ODI) score, the EuroQol-5-dimension-5-level (EQ-5D-5L) questionnaire, and the 10-point pain VAS scale, and demographics and baseline patient characteristics [including age, gender, occupation, comorbidity (diabetes mellitus, hypertension), bone mineral density, body mass index, medical/surgical history, smoking/drinking habits, physical examination, and laboratory test]. The assessor will be blinded to participants’ personal information.

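### The secondary mixed model does not fix how baseline enters the group contrasts for back VAS, leg VAS and EQ-5D; modelling the session score with baseline as a covariate is a free, low-severity improvement

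*Protocol article*

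**What the plan says.** All of this is in the protocol article, Statistical analyses, unless another section is named.

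- For back and leg VAS, ODI, EQ-5D and POSAS over time, "a linear mixed model repeated-measures analysis of variance will be used".
- The levels of the time factor are all postoperative: "Time will be regarded as a categorical variable (at 2 weeks and at 3, 6, and 12 months"), so the preoperative value is not listed as a level of time.
- The factor is to be "analyzed to evaluate serial changes from baseline, within each group, and between the two groups at each session". The response variable (score or change) is not named, and no covariates are listed.
- The only other stated use of baseline is that "we will assess whether the baseline variables of the two groups are visually balanced".
- Baseline values exist. Data collection lists "the Oswestry Disability Index (ODI) score, the EuroQol-5-dimension-5-level (EQ-5D-5L) questionnaire, and the 10-point pain VAS scale" among the preoperative assessments. Table 1 schedules ODI, EQ-5D-5L and VAS at screening, but POSAS only at 12, 24 and 52 weeks.
- Inclusion criteria require radiating leg pain "with a pain score > 4 on a 10-point visual analog scale (VAS").
- The primary analysis is described separately and uses the score itself: "The primary outcome (the ODI score at 12 months post-surgery) will be compared between the two groups".

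**The concern.** One natural reading of the sentence is that the arms are compared on change from baseline at each session, with no baseline term in the model. A change score subtracts the whole baseline value, however weakly that value predicts the score weeks or months after surgery. This has two consequences.

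First, variation in the baseline is carried into the contrast, so intervals are wider than they need be. Second, the arm that happens to start worse tends to show the larger improvement, and a visual check of balance does not remove that.

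Pain and quality of life are the main patient-reported evidence beside the ODI. The only margin in the article is for the ODI, so an imprecise secondary contrast is easily taken as agreement between the procedures.

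If the arms are instead compared on raw scores at each session, the question is only whether baseline values already collected are left unused.

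**Working it through.** **Inputs.** The article gives no precision or power figure for this model, so there is none to reproduce. From Sample size justification: 50 per arm with 20% loss leaves 50 × 0.80 = 40 per arm. The article gives no correlation between baseline and follow-up (ρ), no VAS or EQ-5D SD and no target difference for these outcomes. These are assumptions here: ρ from 0.2 to 0.7, and k = baseline SD ÷ follow-up SD of 1, 0.8 or 0.6.

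**Variances per patient, in units of the follow-up variance.**

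- Change score: 1 + k² − 2ρk, which is 2(1 − ρ) when k = 1
- Raw score: 1
- Baseline-adjusted score: 1 − ρ²

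**Equal SDs (k = 1).** The ratio change ÷ adjusted is 2(1 − ρ)/(1 − ρ²) = 2/(1 + ρ). With 40 per arm, a change analysis is worth 40 × (1 + ρ)/2 adjusted patients per arm.

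| ρ | Variance ratio, change ÷ adjusted | SE excess, change | Worth of 40 per arm | SE excess, raw: 1/√(1 − ρ²) |
|---|---|---|---|---|
| 0.2 | 2/1.2 = 1.67 | 29% | 24 | 2% |
| 0.3 | 2/1.3 = 1.54 | 24% | 26 | 5% |
| 0.5 | 2/1.5 = 1.33 | 15% | 30 | 15% |
| 0.7 | 2/1.7 = 1.18 | 8% | 34 | 40% |

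Change scores are noisier than raw scores only when 2(1 − ρ) > 1, that is ρ < 0.5.

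**Compressed baseline SD.** The entry cut-off may narrow the leg-pain baseline. The ratio change ÷ adjusted is then:

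- k = 0.8: 1.32/0.96 = 1.38 (ρ 0.2), 1.16/0.91 = 1.27 (0.3), 0.84/0.75 = 1.12 (0.5)
- k = 0.6: 1.12/0.96 = 1.17 (0.2), 1.00/0.91 = 1.10 (0.3), 0.76/0.75 = 1.01 (0.5)

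**Power illustration.** Assumed: follow-up VAS SD 2.5, true difference 1.5, ρ = 0.3, 40 per arm, two-sided 5%, normal approximation. The raw variance of the difference is 2 × 2.5²/40 = 0.3125.

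- Change, k = 1: SE = √(1.4 × 0.3125) = 0.66, power 62%
- Raw: SE = √0.3125 = 0.56, power 77%
- Adjusted: SE = √(0.91 × 0.3125) = 0.53, power 80%
- Change, k = 0.6: the variance factor is 1.00, so power equals that of raw scores, 77%

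**Chance imbalance.** Given an observed baseline difference, the change contrast shifts by (ρ/k − 1) per unit of that difference. It over-corrects as long as ρ < k.

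- k = 1: −0.8, −0.7, −0.5 and −0.3 at ρ = 0.2, 0.3, 0.5 and 0.7. Simulated slopes (20,000 trials, 40 per arm) were −0.81, −0.70, −0.49 and −0.30.
- k = 0.6 to 0.8, ρ = 0.2 to 0.5: −0.75 to −0.17.

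The chance baseline difference at 50 per arm has an SD of √(2/50) = 0.20 baseline SDs. With a follow-up SD of 2.5 and k = 0.6 to 0.8, that is 0.3 to 0.4 VAS points. The resulting shift is about 0.17 × 0.3 = 0.05 to 0.75 × 0.4 = 0.3 points.

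**Average behaviour.** In the same simulations (k = 1) the mean change contrast under no effect was about 0, and type I error was 0.048 to 0.052.

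**The case against.** The strongest reply is that the article does not say what the concern needs it to say. It lists no covariates for any model, and a condensed article may leave them to an analysis plan that is not shown. The sentence can also be parsed as changes within groups and scores between groups. Evaluating change is moreover compatible with a baseline-adjusted model, in which the group contrast is the same for score and change. POSAS is in the same sentence and has no preoperative value, so the sentence cannot be a uniform change-score specification. All of this stands. A reader might infer that the plan commits to unadjusted change scores; the documents do not establish that.

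A reader might also infer that selecting patients on leg VAS and then subtracting that VAS biases the comparison through regression to the mean. It does not. The cut-off is applied before randomisation and to both arms, so the regression cancels in expectation. What remains is conditional on the imbalance that happens to occur.

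The size is also open to challenge. The 62% power figure needs equal SDs, which sits badly with an entry rule that narrows the leg-pain baseline. That stands for leg pain. Back pain and EQ-5D have no such entry rule.

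The reply does not remove the case for a change. Under either reading, adjustment is at least as precise, apart from the negligible cost of estimating a slope, and the sentence must be revised for POSAS in any event.

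**Conclusion.** The point holds as a low-severity improvement to secondary analyses. The text ties the mixed model to change from baseline, leaves baseline out of the listed time levels and states no use of it beyond a visual check, while leaving the response variable open.

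- **If the contrasts are unadjusted change scores:** the SE is 29% to 8% larger than with adjustment for assumed correlations of 0.2 to 0.7 and equal SDs. If the leg-pain baseline SD is 0.6 to 0.8 of the follow-up SD, the variance ratio for correlations of 0.2 to 0.5 falls to between 1.38 and 1.01. The contrasts also over-correct for chance baseline differences over these ranges.
- **If they are raw scores:** the loss is small at low correlation (77% versus 80% power at 0.3) and grows as the correlation rises.

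Under neither reading is there bias on average, and type I error is kept. The correlations, SDs and target difference are assumptions, not figures from the article. The primary 12-month ODI comparison is outside the point.

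**What to change.** In Statistical analyses, state that the response in the mixed model is the score at each session. Add the same outcome's baseline value and its interaction with session as covariates, or include baseline as a time level with the arm means constrained equal. For back VAS, leg VAS and EQ-5D, take the between-group difference with its 95% CI at each session from that model. Keep within-group changes as description only. Model POSAS without a baseline term and only at the visits where Table 1 schedules it.

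The cost is one model statement. The VAS and EQ-5D baselines are already collected, and no patients or visits are added. If an analysis plan already specifies this, the article's sentence need only be aligned with it.

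### The post hoc rule for the secondary outcomes is most naturally triggered by time or group effects, neither of which tests whether the groups differ at a given session

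*Protocol article*

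**What the plan says.** The Statistical analyses section of the protocol article plans one model for the repeated secondary measures (back and leg VAS, ODI, EQ-5D, POSAS): "a linear mixed model repeated-measures analysis of variance will be used". Time is categorical, and the levels listed are 2 weeks and 3, 6 and 12 months. The data are to be "analyzed to evaluate serial changes from baseline, within each group, and between the two groups at each session". The sentence then ends with the follow-up rule: "with a post hoc test used for any significant time- and group-differences identified".

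The section does not name a group-by-time term or a joint test of the session contrasts as the condition for follow-up. It does not say whether the post hoc tests are adjusted. The Background credits the endoscopic approach with, among other advantages, "a less painful recovery, and a shorter hospital stay".

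**The concern.** The question asked is whether the arms differ at each session. The trigger, read in the usual way (overall test first, post hoc test second), answers other questions:

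- A time effect asks whether the two arms pooled change over time. Patients enter with leg pain above 4 on the 10-point scale and are then operated on, so change is to be expected whether or not the procedures differ.
- A group effect asks whether the arms differ on average over sessions. A difference present early and gone later is diluted by the later sessions.

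If the first trigger suffices, the overall step gives little protection against false session differences. If the second is needed, a real early difference may never be tested. An early recovery benefit is part of the case for the endoscopic approach and would show mainly in the 2-week scores, so this sentence could decide whether such a benefit is reported, missed or wrongly claimed.

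**Working it through.** The plan gives no error rate or power for these analyses, so there is no stated figure to reproduce.

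**Inputs from the protocol article.** "100 participants will be recruited, with 50 in each group" with 20% loss to follow-up (Sample size justification) gives 50 × (1 − 0.20) = 40 per group. There are four follow-up levels of time (Statistical analyses).

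**Assumptions not in the document.** Unit SD; equal correlation r = 0.3 to 0.7 between visits; a common improvement after surgery of 1.0 to 1.3 SD; an early difference of 0.65 SD. For scale, 0.65 × 17.1 = 11.1 ODI points, if the 12-month SD also applied at 2 weeks.

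**1. What each test examines.** Let d1 to d4 be the between-group differences at the four sessions.
- Session question: is a given d equal to 0?
- Group effect: is (d1 + d2 + d3 + d4)/4 equal to 0?
- Time effect: are the session means, pooled over arms, equal? The d's do not enter as a contrast.
- Group-by-time: are the d's equal to each other?

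Only a joint test that all d's are 0, or direct estimation of each d, answers the session question in full.

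**2. Time effect as trigger, no true difference, unadjusted session tests.** Four independent tests at 5% would give 1 − 0.95^4 = 18.5%. Correlation between visits lowers this. By simulation:

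| Levels of time | Time effect significant | At least one false session difference |
|---|---|---|
| Baseline plus four follow-ups | 100% | 13-18% |
| Four follow-ups, further improvement after 2 weeks | 57-93% | 9-13% |
| Four follow-ups, flat course after 2 weeks | about 5% | about 1% |

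**3. Group effect as trigger, 0.65 SD at 2 weeks only.** The direct contrast has SE = √(2/40) = 0.224, so z = 0.65/0.224 = 2.91. Its power is Φ(2.91 − 1.96) = 0.83, or about 82% with t tests in simulation.

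The group effect over four sessions is 0.65/4 = 0.1625, with SE = √[(2/40)(1 + 3r)/4]:

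| r | SE | z | Power of group test |
|---|---|---|---|
| 0.3 | 0.154 | 1.05 | 18% |
| 0.5 | 0.177 | 0.92 | 15% |
| 0.7 | 0.197 | 0.83 | 13% |

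In simulation, passing both the group test and the 2-week contrast occurs in 9-19% of trials. The lower end arises when baseline is a fifth level. With no loss (50 per group), the direct contrast has 90% power and the group test 15-22%.

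**4. Same trigger, fading difference.** With differences of 0.65, 0.40, 0.20 and 0.10 SD, the average is 1.35/4 = 0.3375 and z = 2.19, 1.91 and 1.71 for r = 0.3, 0.5 and 0.7. The group test then has power of about 59%, 48% and 40%. Passing both tests occurs in about 39-55% of trials (four follow-up levels), a loss of 82 − 55 = 27 to 82 − 39 = 43 points.

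**5. Cost of adjusting instead of gating.** At the strictest Holm step, 0.05/4 = 0.0125, power for the 2-week contrast is Φ(2.91 − 2.50) = 0.66, or about 64% with t tests.

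**The case against.** The strongest reply is that no gate is stated. The sentence first asks for "serial changes from baseline, within each group, and between the two groups at each session" without any condition, and the post hoc clause could apply only to differences already found. It could, for instance, mean pairwise comparisons among the four time levels. That reading is possible. It explains the time part of the clause, but with two arms a post hoc test has nothing left to locate after a session-level group difference. Reading the clause as follow-up of overall effects therefore remains the more natural course. The ambiguity stands and limits how firmly the fault can be put.

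A second reply is that model terms and adjustment are commonly left to an analysis plan, and none is shown here. This stands for adjustment: the article does not say that the post hoc tests are unadjusted, and a Bonferroni correction over four sessions would hold the false-positive rate at about 5% or less per outcome even with the gate always open. It does not remove the objection to the trigger, which the article itself states.

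Three stronger readings are tempting but not supported:
- *The gate always opens.* This needs baseline as a level of time. The article lists only follow-up sessions, and Table 1 shows no baseline POSAS.
- *An early benefit would almost always be lost.* This needs the difference to vanish completely after 2 weeks. The Background gives no size or time course.
- *False positives accumulate over all outcomes and sessions because of this rule.* Such a total assumes that every test is unadjusted, counts the 12-month ODI, which is the primary outcome with its own rule, and mostly reflects the ordinary multiplicity of several secondary outcomes.

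**Conclusion.** The point holds as a badly chosen trigger for secondary analyses, on the most natural reading of an ambiguous sentence. The two harms belong to alternative readings and do not add up.

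- If a time effect suffices and tests are unadjusted, the false-difference rate per outcome is about 9-13% with the listed levels. It is 13-18% if baseline is a level, and near 1% if the course is flat after 2 weeks.
- If a group effect is required, power for 0.65 SD at 2 weeks falls from about 82% to 9-19% for a difference at 2 weeks only, or to about 39-55% if it fades.

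These figures rest on the assumed correlation, effect size and recovery course. That the two effects do not test session differences needs none of those assumptions. The 12-month ODI conclusion is not affected, and the article attaches no confirmatory claim to any session contrast. The change is worth making because it is cheap and bears on how early recovery is reported.

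**What to change.** Replace the post hoc clause. Suggested text:

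*For each outcome the model will contain group, time and group-by-time. The between-group difference at each scheduled session will be estimated from this model with a 95% CI, regardless of the significance of the main effects. Time effects and within-group changes are descriptive and will not decide whether between-group comparisons are made.*

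Add one sentence on the session-level p-values: either label them exploratory, or adjust them over the sessions of that outcome, for example by Holm. The choice is the sponsor's. Adjustment would at worst lower power for the 0.65 SD difference at 2 weeks from about 82% to about 64%; the exploratory label costs no power but supports no formal claim.

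The change uses the planned mixed model and the same data, with no added patients or visits. It should be fixed before unblinded data are analysed.
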